| Research                                                                                                                                                                                                                                                                                                                                                                                                                            |                             |                      |
| Aims iv                                                                                                                                                                                                                                                                                                                                                                                                           |                             |                      |
| To describe the range of airway inflammatory infiltrate in a group of patients with mild to moderate COPD, and to relate that cell picture to the response to ICS therapy over a 6 month period.                                                                                                                                                                                                                                    |                             |                      |
| The Hypothesis is that positive benefit of ICS therapy in COPD patients is most marked in those with the most prominent degree of airway eosinophilia.                                                                                                                                                                                                                                                                              |                             |                      |
| Justification v                                                                                                                                                                                                                                                                                                                                                                                                   |                             |                      |
| This study commenced in Melbourne (Alfred Hospital) in October 2000, and by the end of 2001 we are on schedule to have recruited 20 participants. We are aiming to study approx. 36 individuals in total to give what we believe will be adequate power to detect differences between treatment groups in airway inflammatory markers. We are looking to recruit a further 16 COPD sufferers in Hobart over the first half of 2002. |                             |                      |
| Thus the specific aim of this application is to allow completion of a study that [name] started in Victoria, and now wishes to transfer to Tasmania. From a scientific and clinical perspective the study will give significant insights into the patho-physiology of COPD and the effects of ICS on the patients.                                                                                                            |                             |                      |

|                                                                                                                                                                                                                                                                                                                                                      |          |                 |                                                |
|------------------------------------------------------------------------------------------------------------------------------------------------------------------------------------------------------------------------------------------------------------------------------------------------------------------------------------------------------|----------|-----------------|------------------------------------------------|
| Period of investigation vi                                                                                                                                                                                                                                                                                                         |          |                 |                                                |
| Commencement date                                                                                                                                                                                                                                                                                                                                    | 1.1.2002 | Completion date | 31.12.2002 for the clinical part of the study. |
| Funding vii                                                                                                                                                                                                                                                                                                                        |          |                 |                                                |
| Source/potential source of funding and amount:
£ sterling 67.5 K (approx. \$180K A) from Glaxo Smith Klein: (approx. \$20K will need to go to the Alfred to pay staff continuing to work on the project there.                                                                                                                                    |          |                 |                                                |
| Do the investigators have any financial interest in this project?                                                                                                                                                                                                                                                                                    |          |                 | NO                                             |
| Review of ethical considerations viii                                                                                                                                                                                                                                                                                              |          |                 |                                                |
| Has this protocol previously been submitted to the University Ethics Committee?                                                                                                                                                                                                                                                                      |          |                 | NO                                             |
| Does this project need the approval of any other Ethics Committee?
The Alfred Hospital Ethics Committee, Melbourne.                                                                                                                                                                                                                               |          |                 | YES                                            |
| If 'YES', what is its current status?
The study is still ongoing at the Alfred (see enclosed certificate). Recruitment there will end at the end of 2001 with final bronchoscopy in approx. June 2002. Because of [name] move to Hobart it will be logistically easier to complete the study here with all recruits beyond the end of 2001. |          |                 |                                                |
| Relevant references                                                                                                                                                                                                                                                                                                                           |          |                 |                                                |
| List references                                                                                                                                                                                                                                                                                                                                      |          |                 |                                                |

## B. PROCEDURES

### Detailed proceduresix

#### Outline of Protocol:

- This will be a double-blind, placebo controlled, parallel group study.
- Subjects will be randomised 2:1 to receive active medication (Fluticasone 500 mcg bd) or placebo bd, both given in the same way via identical dry powder, "Diskus" devices for a duration of 6 months.
- After recruitment, but before initiation of randomised therapy, each patient will undergo:
  - Full spirometry with a flow-volume loop, before and after 200 mcg inhaled salbutamol (a  $\beta$  agonist bronchodilator) given via a spacer device.
  - A Quality Of Life Questionnaire (QOL) (St George's Respiratory Questionnaire) will be completed.
  - Induction of sputum (by spontaneous coughing or by our standard laboratory method of nebulisation of hypertonic saline, if necessary).
- At least 48 hours later, standard flexible fiberoptic bronchoscopy will be performed under local anaesthetic, with 6 endobronchial biopsies being taken from around the orifices of middle or lower lobe bronchi, and a standard 3 X 60 ml bronchoalveolar lavage (BAL) will be performed. Before bronchoscopy, 200 mcg of salbutamol and 80 mcg of ipratropium bromide will be given by inhaler. Supplemental oxygen will be given throughout the procedure and oxygen saturation will be monitored using a finger probe from a pulse oximeter.
- At the end of the study period, these four procedures will be repeated ie questionnaire, pulmonary function, sputum collection and bronchoscopy (with the latter at least 48 hours later to avoid any confounding by potential acute cellular changes induced by sputum induction). Study medication will continue until these investigations are complete.

#### Study Visits

##### Recruitment (Visit 1)

This will be via our volunteer database for smokers or ex-smokers with some respiratory symptoms.

- A detailed respiratory and medical history will be taken and physical examination performed.
- An ECG will be performed.
- Spirometry will be undertaken.
- Inclusion and Exclusion criteria will be assessed. If appropriate, the study will be explained in detail, and the explanatory leaflet will be read and discussed before written consent is obtained.
- A blood sample will be obtained for routine full blood count, U&E and creatinine, liver function tests and random glucose.

First Study Visit (Visit 2) usually within 2 weeks of recruitment and following at least 1 week of run-in during which a symptom diary card will be maintained to collect data on daily symptom scores and sputum produced.

- The subject's clinical stability will be checked.
- The QOL (St GRQ) will be delivered, spirometry performed.
- Sputum will be collected and sent to the research lab for processing.
- A bronchoscopy (Visit 3) will then be arranged within approximately one week, but at least 48 hours later.
- Study medication will then be given to the patient according to a randomisation schedule held in pharmacy.

Intermediate check visits (Visits 4 and 5), at 2 month and at 4 months. The subject will be asked to attend the laboratory every 8 weeks ( $\pm 2$  weeks) to assess well being and check on compliance with study medication. Occurrence of any exacerbations will be recorded. New inhaler devices will be prescribed.

If an exacerbation were to occur in the intervening time, the patient will be asked to contact the Research Laboratory. These exacerbations occur commonly in COPD and are defined as worsening of symptoms requiring additional medication, either with an antibiotic or oral

Prednisolone (a corticosteroid) or both. The patient will be given advice about the best course of action – either to visit the General Practitioner, or if the patient prefers to attend the research laboratory for medical review.

#### Final visit

Two weeks before the expected completion of the study, each subject will be contacted by phone to check on wellbeing, and will then be sent a diary card to collect data over 1 week on daily symptoms and sputum production. At the end of 6 months (Visit 6) of study medication, each subject will return to the laboratory for repeat QOL questionnaire, spirometry and sputum collection, and after a period of at least 48 hours, but within approximately 1 week bronchoscopy will be performed, (Visit 7) as before. Any exacerbations in the previous 2 months will be recorded.

Study medication will be ceased. Approximately 1 week later the patient will be phoned to check on well being, and if there is any deterioration a visit to the laboratory will be arranged at the patient's convenience, for full clinical review.

#### Study outcome measures/efficacy measurements

- Changes in the QOL measure and spirometric values (large and small airway flow rates)
- Sputum neutrophil and eosinophil percentage counts
- Bronchoalveolar lavage cell differential counts and FACS analysis (lymphocyte and macrophage subtypes and activation markers). BAL supernatant will be stored for cytokine and chemokine assays and assay of selected mediators, eg ECP, neutrophil elastase and myeloperoxidase.
- Airway biopsies: the initial emphasis will be on acute and chronic cellular inflammation: numbers of eosinophils, neutrophils, lymphocytes and macrophages and activation markers HLADR and CD25 but with the potential for later study of indices of scarring and "remodelling" of the airway wall ie collagen I, III and V deposition, epithelial integrity, subepithelial basement membrane thickness and degree of vascularity in the subepithelial lamina propria area (by collagen IV staining).

**NB** Over the past 15 years of research into airway pathology using fibre-optic bronchoscopy, we have developed a wide range of end points with which to assess both BAL and biopsy material. The degree to which we can fully utilise the material will depend upon funding over the next three years. However, we already have sufficient funding to allow assessment of acute and chronic cellular infiltrates in the airway, which is our primary pathological endpoint. Further grant applications will be developed over the next 12-18 months, based upon this study protocol, the extremely valuable biological material obtained and our extensive "track record" in this field of research (see references).

#### Statistical Analysis

At the end of the study we will intend to have 24 paired sets of data in volunteers treated with active intervention (Fluticasone) and 12 in placebo treated controls.

There will be 4 main approaches to analysis:

- Baseline bronchoscopic data as a whole will be analysed against our current historic normal control data, of which we have large numbers both for airway biopsy (n=24) and BAL (n=36). This will give us excellent power to detect even subtle changes within COPD cell profiles (and later structural components).
- The placebo control material will be used to establish stability over time in biological signals and to establish coefficients of repeatability for cellular indices. Paired analysis within the actively treated group will be undertaken to indicate which cellular populations or activation markers may be susceptible to change with ICS, and then changes over time in these indices will be compared with respective changes in the placebo treated control material. We have previously published repeatability data in chronic stable asthmatics, and done similar calculations in post lung transplant airway samples, which indicate that optimal power for detecting changes with time is achieved with approx. 15 data pairs for most cell lines. With the numbers available in this COPD study, we therefore have substantial "reserve".
- The central analysis will focus on the ICS treated group and use changes over time in both cellular indices (in BAL and biopsies) and clinical and physiological end points, and undertake regression analyses to define which, if any, of the cellular changes are related to clinical and/or physiological improvements.

- We will perform post-hoc analyses in selected sub-groups, namely:
  - a) those in whom regular sputum production is a feature.
  - b) those with above normal airway eosinophils.
  - c) those with more or less severe lung function abnormalities (best and worse 10) to define whether ICS have more benefit in these patients than in COPD in general.

This will be a large and complex data set, but we have extensive experience in relating clinical, physiological and bronchoscopic pathological end points. We have developed close collaboration with [name] and [name], our statistical advisers at Monash University, and they will again by providing assistance with this study.

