## SUBJECTS

### Selection of subjects x

#### Inclusion criteria:

- Age 40-70 years
- 36 subjects with smoking-related COPD to complete the study, which will mean likely need for initial recruitment of up to 45 patients (both male and female will be included).
- Minimum of 15 pack-year history of cigarette smoking. Either current or ex smokers.
- FEV1 40% to 80% predicted and/or FEF50<50% with FER (ratio of FEV1 to FVC)  $\leq 70\%$  post bronchodilator and definite scalloping out of the descending limb of the flow-volume loop on spirometry. Absolute FEV  $\geq 1.5$  litres.
- Bronchodilator therapy with a short acting beta agonist prn and anticholinergics in stable doses will be allowable.

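### The power claimed for comparing baseline COPD samples with historic normals is unquantified, and the protocol's own sample sizes do not support it

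*Protocol*

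**What the plan says.** Under Statistical Analysis, the first of four main approaches reads: "Baseline bronchoscopic data as a whole will be analysed against our current historic normal control data". The normals number 24 for airway biopsy and 36 for BAL, which the protocol describes as large. It then concludes: "This will give us excellent power to detect even subtle changes within COPD cell profiles", and extends the claim in parentheses to structural components to be studied later. No difference, SD, significance level or numerical power accompanies the statement.

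The number of COPD subjects at baseline has to be read from two places. Statistical Analysis says "we will intend to have 24 paired sets of data in volunteers treated with active intervention (Fluticasone) and 12 in placebo treated controls", which makes 36 completers. The Inclusion criteria mention a "likely need for initial recruitment of up to 45 patients". The first bronchoscopy comes before study medication, so the baseline sample could lie anywhere from 36 to 45.

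The COPD subjects are 40 to 70 years old, and the smoking criterion is "Minimum of 15 pack-year history of cigarette smoking. Either current or ex smokers". The protocol does not give the age or smoking status of the normals, and does not say whether the comparison will be matched or adjusted.

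**The concern.** The sentence promises high power for small differences from groups of a few dozen. Groups of that size normally give good power only for medium-to-large differences. The statement is made in the protocol itself, so it is not a detail left for a later analysis plan.

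The comparison serves the first stated aim, which is to describe the airway infiltrate in mild to moderate COPD. A reader who trusts the power statement would give too much weight to a cell type that shows no significant difference from normal. A related question is what a difference would mean, since the COPD group is defined partly by age and smoking and the comparator is not described on either.

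**Working it through.** **Inputs from the protocol.** Normals: 24 (biopsy) and 36 (BAL), from Statistical Analysis. COPD subjects at baseline: 36 (24 + 12 completers, Statistical Analysis) up to 45 (Inclusion criteria).

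**Assumptions, because the protocol gives none.** Two-sided 5% test of two means, equal SDs, differences expressed in SD units (d). There is no stated power figure to reproduce.

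**Formulas.** With n₁ normals and n₂ COPD subjects, the standard error of the difference in SD units is SE = √(1/n₁ + 1/n₂). By the normal approximation, the difference detectable with 80% power is (1.960 + 0.842) × SE. The noncentral t version uses n₁ + n₂ − 2 degrees of freedom and noncentrality d/SE.

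**Example, biopsy, 36 v 24.** SE = √(1/24 + 1/36) = 0.264, so the detectable difference is 2.802 × 0.264 = 0.738 SD, or 0.751 SD by noncentral t. At d = 0.3, d/SE = 1.138, and power ≈ Φ(1.138 − 1.960) = Φ(−0.822) = 20.6%, or 20.1% by noncentral t.

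| Sample | Normals | COPD | SE | 80% power, normal approx. | 80% power, noncentral t | Power at 0.3 SD | Power at 0.5 SD | Power at 0.8 SD |
|---|---|---|---|---|---|---|---|---|
| Biopsy | 24 | 36 | 0.264 | 0.738 SD | 0.751 SD | 20.1% | 46.3% | 84.7% |
| Biopsy | 24 | 45 | 0.253 | 0.708 SD | 0.718 SD | 21.5% | 49.6% | 87.7% |
| BAL | 36 | 36 | 0.236 | 0.660 SD | 0.670 SD | 24.1% | 55.3% | 91.7% |
| BAL | 36 | 45 | 0.224 | 0.626 SD | 0.634 SD | 26.3% | 59.8% | 94.2% |

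The three power columns are by noncentral t. For 90% power with 36 COPD subjects, the detectable differences are 0.869 SD (biopsy) and 0.775 SD (BAL).

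**More favourable variants.**
- With 45 COPD subjects and a one-sided 5% test (normal approximation), the detectable differences are 0.628 and 0.556 SD, and power at 0.3 SD is 32% and 38%.
- The normals set a floor. With an unlimited number of COPD subjects, SE = √(1/24) = 0.204 or √(1/36) = 0.167, so 80% power still needs 2.802 × 0.204 = 0.57 SD or 2.802 × 0.167 = 0.47 SD.

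**Less favourable variants (36 COPD subjects, normal approximation).**
- If the COPD SD is 1.5 to 2 times the normal SD, the detectable difference is 0.90 to 1.10 normal SDs (biopsy) and 0.84 to 1.04 (BAL).
- With a Bonferroni level of 0.005 for ten indices, it is 0.96 and 0.86 SD. Ten is illustrative; the protocol fixes no number.

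**Size needed for small differences.** Per group, n = 2 × 2.802² / d². At d = 0.3 this is 15.70/0.09, about 175; at d = 0.2 it is 15.70/0.04, about 393.

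**The case against.** The strongest defence is that the protocol never defines a subtle difference, and without an effect size, SD or significance level there is no figure to contradict. That stands to this extent: the statement should be called unsupported, not proven false. It does not rescue the statement, because even the most favourable variant above leaves power at 0.3 SD below 40%. The sizes do serve large differences well (about 85% power for biopsy and 92% for BAL at 0.8 SD with 36 COPD subjects), but such differences are not subtle.

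It is also fair to say that the comparison is non-randomised and does not carry the trial. The Justification section relates the total of 36 to differences between treatment groups, and the analysis called central is a regression within the steroid-treated group. Neither depends on this sentence.

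A reader might go further on three counts, and the document does not support any of them:
- That the comparison is confounded by smoking and age. The normals are not described, so they could be of similar age or include smokers. Smoking is also part of how the COPD population is defined.
- That the plan commits to an unadjusted analysis. It states no model either way, and covariates may be specified in an analysis plan not seen here.
- That non-significant cell types will be reported as normal. No rule for interpreting null results is given.

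**Conclusion.** The power statement should not stand. Across the plausible baseline numbers, 80% power is reached only at about 0.72 to 0.75 SD for biopsy and 0.63 to 0.67 SD for BAL. A difference of 0.5 SD would be detected about 46 to 50% of the time in biopsies and 55 to 60% in BAL. These figures rest on a two-sided 5% test, equal SDs and no multiplicity allowance. More variable COPD data, or a correction for several markers, would make them worse.

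On attribution, the supportable conclusion is narrower. The age and smoking status of the normals are not documented, so a difference cannot yet be assigned to COPD as distinct from smoking or age. That is a risk the protocol leaves open, and no imbalance has been shown. The reach is limited to this descriptive comparison.

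**What to change.** Replace the power sentence with one along these lines: *With 36 to 45 COPD subjects at baseline, a two-sided 5% test and equal SDs, the comparison has 80% power for differences of about 0.72 to 0.75 SD in biopsy indices (24 normals) and 0.63 to 0.67 SD in BAL indices (36 normals), without allowance for multiple markers; smaller differences cannot be excluded.* Report a confidence interval for every comparison.

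Describe the result as smoking-related COPD versus these historic normals, and report the normals' age and smoking history where known. Adjust for age and smoking only if the control records hold them and the two groups overlap. If the normals have little or no smoking history, adjustment would be extrapolation, and the comparison should be labelled descriptive.

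The cost is a change of wording and a less favourable power statement. No extra subjects or procedures are needed.

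### The protocol compares airway markers with placebo only after an uncontrolled before-after look in the ICS arm, which can hide effects seen as placebo change and inflates small differences

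*Protocol*

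**What the plan says.** The Outline of Protocol describes a randomised controlled design: "This will be a double-blind, placebo controlled, parallel group study" and "Subjects will be randomised 2:1 to receive active medication". The Justification section bases the total of about 36 subjects on power to find differences between the treatment groups in airway inflammatory markers. The outcome measures section names cellular infiltrate in the airway as the primary pathological endpoint.

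The Statistical Analysis section plans for "24 paired sets of data in volunteers treated with active intervention (Fluticasone) and 12 in placebo treated controls". Its second approach has three parts:

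- Placebo as a reference for stability and repeatability: "The placebo control material will be used to establish stability over time in biological signals".
- A within-arm step: "Paired analysis within the actively treated group will be undertaken to indicate which cellular populations or activation markers may be susceptible to change with ICS".
- A between-arm step: "and then changes over time in these indices will be compared with respective changes in the placebo treated control material".

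The section describes no other fluticasone-versus-placebo comparison of cellular markers. The third approach, which the protocol calls central, is a regression analysis focused on the ICS arm.

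**The concern.** The within-arm step ignores the randomised control, yet it appears to decide which markers the control is used for. Three consequences need checking.

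1. A marker that stays level on fluticasone while it changes on placebo shows no within-arm change. It would not be carried forward, although the treatment difference is real.
2. The two steps share the fluticasone data. A marker carried forward because its fluticasone change happened to be large brings that chance excess into the comparison with placebo.
3. A time trend common to both arms can earn a marker the label of being susceptible to ICS before placebo has been consulted.

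At stake is the reading of the main biological endpoint, for which the randomised comparison is the only protected evidence of a drug effect.

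**Working it through.** **Inputs from the protocol.** Allocation is 2:1 with 36 completers, so 36 × 2/3 = 24 and 36 × 1/3 = 12. This reproduces the stated numbers of pairs.

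**Assumed inputs.** The protocol gives no significance level, SD of change or effect size. I take two-sided 0.05 at each step, normally distributed changes with SD 1 in both arms, and true changes from 0 to 1 SD. All effects below are in SD units of change.

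**Tests.** Step 1 is a paired t-test on the fluticasone changes: t = mean × √24 / s, with 23 df. A marker passes when its observed mean change exceeds about 2.07/√24 = 0.42 SD. Step 2 is a two-sample t-test, with the standard error of the difference equal to √(1/24 + 1/12) = √(1/8) = 0.354 SD and 34 df. The correlation between the fluticasone mean and the between-arm difference is √((1/24)/(1/8)) = 0.577, so selection at step 1 carries into step 2. The two-step procedure was simulated with 400,000 trials per scenario and compared with a direct between-arm test of every marker.

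**(a) Effects seen as placebo change**

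| ICS change | Placebo change | Passes step 1 | Detected, direct | Detected, two steps |
|---|---|---|---|---|
| 0 | −0.5 | 5% | 28% | 2.2% |
| 0 | −0.8 | 5% | 60% | 2.8% |
| 0 | −1.0 | 5% | 78% | 3.3% |
| +0.25 | −0.75 | 22% | 78% | 21% |

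The last row shows that the loss does not require a completely flat fluticasone arm.

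**(b) Estimates after screening, placebo stable**

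| True difference | Mean difference among screened markers | Detected, direct | Detected, two steps |
|---|---|---|---|
| 0.25 | 0.51 | 10% | 6% |
| 0.5 | 0.61 | 28% | 25% |
| 0.8 | 0.82 | 60% | 59% |
| 1.0 | 1.00 | 78% | 78% |

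Inflation is about twofold at 0.25 SD and 22% at 0.5 SD (0.61/0.5), and is essentially gone by 0.8 SD.

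**(c) No drug effect, the same drift in both arms**

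| Common drift | Flagged at step 1 | False positive among flagged | Passes both steps |
|---|---|---|---|
| 0 | 5% | 25% | 1.2% |
| 0.2 | 16% | about 11% | 1.8% |
| 0.3 | 29% | 7.5% | 2.2% |
| 0.5 | 65% | 4.5% | 2.9% |

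The two middle columns move in opposite directions. The 25% figure belongs to the case where few markers are flagged, and where 65% are flagged the conditional error is nominal. With no drift and no effect, the mean spurious difference among flagged markers is 0.46 SD in the flagged direction. The direct test rejects in 5% of trials in every row.

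**The case against.** The strongest reply is that the text sets no gate. It gives no p-value or selection rule and speaks of indicating what may be susceptible. The phrase about these indices could refer to the cellular indices of the preceding sentence, meaning all of them. On that reading nothing is selected and the harms above do not arise. This stands as a limit on certainty. It does not remove the need for a change, because the order of the sentence favours the narrower reading and nothing else in the section provides for comparing all markers.

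A reader might infer that the plan credits shared time trends to ICS in its final results. The documents do not support that. The second step is the randomised comparison and removes most of any common trend; passing both steps stays below 5% per marker. The trend misleads mainly through the step 1 label.

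A reader might also infer that season is built into the Hobart data, since those 16 of 36 subjects are recruited "over the first half of 2002" and resampled six months later. A January entrant goes from summer to winter and a June entrant the reverse, so the shifts can partly cancel, and Melbourne recruited from October 2000 to the end of 2001. Regression to the mean is likewise weakly supported: entry rests on spirometry and history, not on cell counts.

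Two further points stand in part. The 1 SD placebo shift is an assumption, and a paired test on 12 placebo pairs would itself notice such a shift about 88% of the time; that would raise a question but would not replace the between-arm estimate. And if only significant results are considered, a direct test also exaggerates: at a true 0.5 SD the mean significant difference is 0.91 SD direct and 0.92 SD after two steps. The inflation specific to the screen is that of all screened estimates, in table (b).

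**Conclusion.** The point holds on the natural reading of the second approach. The main harm is missed effects: detection drops from 78% to 3% when ICS is flat and placebo shifts 1 SD, and from 78% to 21% in the mixed case. The second is inflated estimates for screened markers when effects are small, with a conditional false-positive rate of 25% if there is neither drift nor effect, falling towards nominal as drift grows. When placebo is stable and the true effect is 0.8 SD or more, the sequence does almost no damage.

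It would be too strong to say that the overall error rate is inflated, or that unflagged markers are certain never to be compared. All sizes rest on the assumed 0.05 gate, SD of 1 and normal changes; a looser gate would shrink them.

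**What to change.** Reword the second approach to say that the fluticasone-versus-placebo comparison of change, adjusted for the baseline value, will be made for every cellular index in the outcome measures section that is assayed, whatever the within-arm result, and reported with a confidence interval. State that within-arm paired changes are descriptive and do not select indices. Using the placebo arm for stability and repeatability can stay as it is.

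The cost is wording only; no sample, visit or procedure changes. More between-arm tests will be reported, so they should be labelled exploratory or controlled for multiplicity. Adding site and current smoking as covariates is optional and costs two degrees of freedom.
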